### Surgical interventions

#### Active intervention: interlaminar full-endoscopic discectomy

The technical procedure for interlaminar full-endoscopic discectomy [28], including recent updates, is well described in the literature [3, 4, 29–33]. The spine surgeons are familiar with this approach due to its similarity to the conventional posterior approach, except for creating a working channel for the endoscope and spinal instrument [3, 4, 32]. The procedure is performed under general or spinal anesthesia with the participant in the prone. The surgical table is bent approximately at the level of the lower lumbar spine, with appropriate flexion of the hip and knees; this position widens the interlaminar window [3, 4]. A 5–7-mm skin incision is created at the entry point for the working channel, approximately 1 cm from the midline, at the level of the symptomatic herniated disc, visualized by intraoperative C-arm anteroposterior fluoroscopy imaging, as previously described [30]. The working channel is inserted and positioned at the target point over the ligamentum flavum with sufficient subdermal fascia dissection. After optimal positioning of the working channel at the targeted location, the endoscope is inserted into the working channel under sufficient irrigation along with saline solution [3, 4, 30, 32, 33].

Surgery is performed by inserting the required spinal surgical instruments (bipolar radiofrequency cauterization devices, burrs, Kerrison punches, and pituitary rongeurs) through the working channel. The paravertebral muscle is coagulated to identify the border of the interlaminar window [3, 4, 30]. The ligamentum flavum is either resected using a punch or split using a probe at the level of the tip of the descending facet [3, 11, 30, 31]. The discectomy is performed in a fully endoscopic, minimally invasive manner (Fig. 2).

**Fig. 2 Fig2:**
[figure not shown]
**a** Operative field of interlaminar full-endoscopic discectomy. **b** Intraoperative endoscopic view, showing the disc space and decompressed left S1 nerve root

#### Control intervention: conventional microscopic discectomy

For microscopic discectomy, the target lumbar level of symptomatic disc herniation is again visualized under C-arm intraoperative fluoroscopy, and a 2.5-cm midline incision is made over the target level. The paraspinal muscle is detached from the spinous process and lamina, and detached muscle towing is performed in a minimally invasive fashion through the small skin incision under microscopic visualization. Minimal laminotomy is then performed using a burr, and Kerrison punches under microscopic visualization. After the partial removal of the ligamentum flavum under the lamina, discal impingement of the spinal roots and dura is verified. The spinal nerve root is retracted using a root retractor, and the herniated disc is removed by pituitary forceps below the retracted nerve root. Following discectomy, the surgical field is verified for any remnant disc. This marks the end of the procedure.

### Measured outcomes

A complete description of the time-points at which the data on the primary and secondary outcomes will be collected is provided in Table 1.

**Table 1 Tab1:** Evaluation schedule

Visit type	Screening	Surgical intervention	Follow-up			
Visit	1	2	3	4	5	6
Visit week	4–0 weeks	0–2 days	2 weeks	12 weeks	24 weeks	52 weeks
			± 5 days	± 4 weeks	± 8 weeks	± 8 weeks
Informed consent	■					
Demographics^*^	■					
Inclusion/Exclusion	■					
Randomization		■				
Surgery		■				
MRI (or CT)†	■	■				
Simple radiographs	■		■	■	■	■
ODI	■		■	■	■	■
EQ-5D-5L	■		■	■	■	■
VAS	■		■	■	■	■
POSAS				■	■	■
Other survey‡			■	■	■	■
Adverse events		■	■	■	■	■

POSAS, Patient and Observer Scar Assessment Scale

^*^Baseline patient characteristics, including age, gender, occupation, comorbidity (diabetes mellitus, hypertension), bone mineral density, body mass index, medical/surgical history, smoking/drinking habits, physical examination, and laboratory test

^†^CT imaging used when MRI cannot be performed

^‡^Including surgery satisfaction, walking time/distance, and return to daily activities after surgery

#### Primary outcome

The primary outcome will be the efficacy of the surgical intervention (interlaminar full-endoscopic discectomy or conventional microscopic discectomy), measured using the Oswestry Disability Index (ODI) score at 12 months [34, 35]. The ODI is the most valuable tool for evaluating patient-reported functional outcomes for lumbar spinal disabilities in a clinical setting [34, 35]**.** The ODI evaluates the level of function on activities of daily living for patients with low back pain across the following 10 areas: pain intensity, personal care, lifting, walking, sitting, standing, sleeping, sex life, social life, and traveling. Each section of the ODI is scored on a 5-point scale, with a score of 5 representing the most severe disability. The total ODI score is used for analysis, calculated as the sum of the scores across the 10 areas divided by the total possible score, and expressed as a percentage (i.e., multiplied by 100). For all unanswered questions, the total possible score is reduced by five. The highest score is recorded if the participant checks more than one answer. The ODI will be administered and scored by the assessor, which will be recorded in the eCRF system.

#### Secondary outcomes

The following secondary outcomes will be included in the analysis: patient-reported outcomes, clinical outcomes, radiographic outcomes, and adverse events. Patient-reported outcomes are as follows: (1) presence and severity of low back pain and pain radiating to the lower-extremities, measured using a 10-point VAS score, ranging from “0” (no pain) to “10” (severe pain); (2) quality of life (QOL), measured using the EuroQol-5-dimension-5-level (EQ-5D-5L) questionnaire, which consists of five questions, with the total score ranging between “0” and “1,” with a higher score indicating a better QOL [36]; (3) satisfaction with the surgery; and (4) walking distance/time and time to return to daily activities after surgery. The following clinical outcomes will be measured: (1) postoperative surgical scarring, measured using the Patient and Observer Scar Assessment Scale (POSAS; version 2.0), which consists of six items scored on a 10-point system, with a score of “6” (i.e., a score of ‘1’ on each item) indicative of normal skin and a score of “60” (i.e., a score of “10” on each item) indicative of the “worst scar imaginable” and (2) surgery-related variables, namely postoperative drainage (mL), operative time (min), duration of hospitalization (h), and postoperative creatine kinase. The following radiographic outcomes will be obtained: (1) the extent of disc removed and injury to the facet joint, measured using postoperative MR or CT images, and (2) simple radiographs will be used for measuring other complications during the follow-up period. We will use the Carragee classification to evaluate MRI outcomes [37]. The dimensions of the disc on an axial image with the greatest encroachment will be directly measured [37]. The area of the herniated disc encroaching into the canal space (disc area) and hemiarea of the herniated disc (hemidisc area) will be calculated by using the following linear measurements on pre- and postoperative MRIs: 1) the longest anterior–posterior disc length and 2) width of the herniated disc at the midpoint of its posterior protrusion (mid anteroposterior disc width) [37]. To evaluate facet joint injury, the width of the medial facet on an axial image with the greatest width of the facet joint will be measured on pre- and postoperative MRIs [37]. Radiographs will be obtained in the anteroposterior, lateral, flexion, and extension views, and spondylolisthesis and segmental instability at the target surgical level will be scored based on these images. Radiographs will also be obtained at baseline and during each follow-up session. Preoperative spinal MRI will be systematically conducted in the sagittal and axial planes to determine the type and location of the disc herniation. Safety will be evaluated based on the number of adverse events and the severity of these events, as well as surgery-related events. Adverse events, including postoperative infection and recurrence of disc herniation, will be recorded at each follow-up session. Recurrence of disc herniation will be diagnosed on MRI when newly developed radiculopathy is suspected during the follow-up period. Adverse events will be reported to the surgeon by the participant or the assessor and will be recorded in the electronic database. The data on patient-reported outcomes, clinical outcomes, plain radiographs, and adverse events will be collected at baseline and at each follow-up session (2 weeks and 3, 6, and 12 months after surgery). The assessor will manage and evaluate outcomes and record them in the eCRF system (Table 1).

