### Randomization and follow-up

After completing the baseline assessments, participants will be block-randomized into either the control (microscopy) or intervention (endoscopy) group, using a 1:1 allocation ratio, with a block size of four. The randomization list will be computer-generated and integrated into a web-based electronic case report form (eCRF) platform (iCReaT; internet-based clinical research and trial, icreat.nih.go.kr). The central randomization will be conducted by a contract research organization company (Helptrial), and the data will be accessible only to the trial’s authorized researchers. The randomization of patients to either the control or intervention group will be presented to the study surgeons in each participating hospital using consecutively numbered opaque envelopes.

To evaluate the primary and secondary outcomes, follow-up assessments will be planned for each participant at 2 weeks and at 3, 6, and 12 months after surgery. An independent researcher will perform the assessments at each time-point of follow-up. Phone interviews will be used under unavoidable circumstances where in-person follow-up is not possible (Fig. 1).

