
### Statistical analyses

All statistical analyses will be performed using SAS Enterprise Guide 4 (SAS Institute Inc., Cary, North Carolina, USA). Before performing the main comparative statistical analyses, we will assess whether the baseline variables of the two groups are visually balanced.

An intention-to-treat strategy will be implemented in this non-inferiority RCT. In addition, sensitivity analyses using per-protocol and As-treated will be conducted to identify the deviations from the original assignments during randomization. Participants excluded before or after surgery will not be considered for analysis or replaced, thus avoiding the risk of bias in allocation concealment.

The primary outcome (the ODI score at 12 months post-surgery) will be compared between the two groups. Interlaminar full-endoscopic discectomy will be considered equivalent to microscopic discectomy concerning surgical outcomes if the 95% confidence interval (CI) of the treatment difference value of the Interlaminar full-endoscopic discectomy group is included in the equivalence limit of 12.8 points.

To analyze the time-dependent change in secondary patient-reported and clinical outcomes (i.e., VAS pain scores for the back and lower extremities and ODI, EQ-5D, and POSAS scores), a linear mixed model repeated-measures analysis of variance will be used. Time will be regarded as a categorical variable (at 2 weeks and at 3, 6, and 12 months) and analyzed to evaluate serial changes from baseline, within each group, and between the two groups at each session, with a post hoc test used for any significant time- and group-differences identified.

Chi-square test for categorical variables and Student’s t-test for continuous variables will be used to analyze other clinical and radiographic outcomes and adverse effects between the two groups. The collected data’s distribution will be evaluated using the Shapiro–Wilk test, with a two-sided P-value. Normally distributed continuous variables will be reported as means and standard deviations (SDs), with non-normally distributed continuous variables reported as medians and interquartile ranges. Categorical variables will be reported as count and percentage (%).

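### The extent of disc removal is compared by a t-test that ignores the preoperative disc area already measured, which costs precision, possibly a lot, depending on a derivation the article does not give

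*Protocol article*

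**What the plan says.** Under Secondary outcomes, the protocol article names "the extent of disc removed and injury to the facet joint, measured using postoperative MR or CT images". Disc area and hemidisc area "will be calculated by using the following linear measurements on pre- and postoperative MRIs". The same section adds "We will use the Carragee classification to evaluate MRI outcomes". It does not say whether the extent removed is the absolute difference between the two areas, a percentage, or the area that remains.

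Under Statistical analyses, Student's t-test "for continuous variables will be used to analyze other clinical and radiographic outcomes and adverse effects between the two groups". The linear mixed model is reserved for "VAS pain scores for the back and lower extremities and ODI, EQ-5D, and POSAS scores", so the imaging measures fall to the t-test, and no covariate is named for it. Allocation is randomized, "using a 1:1 allocation ratio, with a block size of four". On baseline comparability the section says only that "we will assess whether the baseline variables of the two groups are visually balanced".

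**The concern.** Each patient has the same quantity measured before and after surgery, yet the stated test does not use the preoperative value. How much this matters depends on which variable is tested.

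If it is preoperative minus postoperative area, the result is bounded by the size of the herniation. Two patients with equally complete decompression can have very different amounts removed. Inclusion criteria admit protruded, extruded and migrated herniations, so some spread in preoperative area is to be expected. That spread enters the standard error as noise.

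If the variable is the residual area, the preoperative value still carries some information, but less is lost by leaving it out.

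The Background section builds the trial's argument on similar neural decompression by the two techniques. In a trial that hopes to show similarity, an imprecise imaging comparison that finds no difference is easily read as support.

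**Working it through.** **Inputs.** The article gives 50 per group (Sample size justification). That figure was derived for the ODI, and there is no stated figure for disc area to reproduce. Using 50 here is reasonable because Table 1 places postoperative imaging at the surgical visit (0–2 days), before most loss to follow-up. Everything else is assumed: preoperative SD 40 mm², postoperative SD 15 mm², correlation r = 0.3, and a true excess of 8 mm² residual disc in one arm. With equal preoperative size, that is also 8 mm² less removed.

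**Standard error of the arm difference**, SE = √(2 × Var / 50):

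- Absolute difference: Var = 40² + 15² − 2 × 0.3 × 40 × 15 = 1600 + 225 − 360 = 1465; SE = 7.66 mm².
- Residual area, t-test: Var = 15² = 225; SE = 3.00 mm².
- Residual area, ANCOVA: Var = 15² × (1 − 0.3²) = 204.75; SE = 2.86 mm².

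**Power at two-sided 5%**, approximately Φ(8/SE − 1.96):

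- Absolute difference: 8/7.66 = 1.04, power about 18%.
- Residual area, t-test: 8/3.00 = 2.67, power about 76%.
- Residual area, ANCOVA: 8/2.86 = 2.80, power about 80%.

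**Chance imbalance.** The SE of the arm difference in preoperative area is 40 × √(2/50) = 8 mm². An imbalance of that size shifts the expected absolute difference by 8 × (1 − 0.3 × 15/40) = 7.1 mm², but the residual area by only 8 × 0.3 × 15/40 = 0.9 mm².

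**Sensitivity to the SDs and correlation.** Write s for postoperative SD divided by preoperative SD. The share of variance of the absolute difference explained by preoperative area is (1 − rs)² / (1 + s² − 2rs). For r from 0 to 0.7:

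- s = 0.2 to 0.3: 91% to 97%
- s = 0.5: 75% to 80%
- s = 0.7: 51% to 67%
- s = 1.0: 15% to 50%

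Over the same grid the ANCOVA variance is 3% to 85% of the variance of the absolute difference. For residual area the ratio of ANCOVA to t-test variance is 1 − r², so the small loss above belongs to r = 0.3 and grows with a stronger correlation.

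**Second model.** A simulation (40 per arm, 10,000 runs) took preoperative area as lognormal and let each patient lose a fraction of it, nominally 65% against 75% on average. Its middle case had coefficient of variation 0.4 and SD of the fraction 0.2. Power there was 23% for the absolute difference, 41% for residual area by t-test, 52% for ANCOVA and 58% for a t-test on the fraction removed. Across coefficients of variation 0.2 to 0.6 and fraction SDs 0.1 to 0.3, the absolute difference gave 11% to 72%, ANCOVA 24% to 99%, and the fraction removed 30% to 99%. With equal removal in both arms, the t-test on the absolute difference rejected in 4.5% to 5.0% of runs and the mean arm difference was about zero.

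**The case against.** The strongest objection is that the article writes no subtraction anywhere. It speaks of measurement on postoperative images and of areas calculated on both sets of MRIs; residual area, percentage removed and absolute difference all fit. A reader might infer that the outcome is a before-minus-after difference that mainly reflects how large the herniation was. The documents do not support that as fact: the derived variable is undefined, and the variance share behind the word mainly depends on SDs they do not give. This stands, so the point must be conditional.

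A reader might also infer that a chance difference in herniation size would bias the comparison. It would not. Randomization balances preoperative size in expectation, the t-test's standard error already allows for imbalance, and the simulation found the nominal error rate. This stands too: what is lost is precision.

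Nor can the area comparison be called the trial's only direct evidence on decompression, since MRI outcomes are also evaluated by the Carragee classification. The primary outcome is the ODI at 12 months, and no margin or decision rule hangs on disc area. A t-test on the fraction removed can do about as well as ANCOVA, so ANCOVA is not the only sound choice.

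Finally, derivations and covariates for a secondary imaging variable are often left to the full protocol or SAP, and a missing derivation alone would be no finding. This stands only in part: the article itself states the test for these outcomes, and that stated choice leaves out a baseline value the trial collects.

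**Conclusion.** The point holds as a minor one about precision. The stated t-test is valid but does not use the preoperative area. Under the assumed inputs (SDs 40 and 15 mm², r = 0.3, 50 per arm, 8 mm² effect), the loss against ANCOVA is large if the absolute difference is tested (18% against 80% power) and small if the residual area is tested (76% against 80%). The first contrast should not be quoted as the trial's power, because it rests on one of several possible readings and every disc-area input is an assumption. The gain shrinks as the residual area comes to vary as much as the preoperative area. Whatever the SDs, an absolute difference would not answer how completely each technique clears the herniation.

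**What to change.** In Secondary outcomes, define the analysed variable as the postoperative residual disc area, and likewise the residual hemidisc area. In Statistical analyses, compare each between arms by ANCOVA with the corresponding preoperative area as covariate, and report the adjusted mean difference with its 95% CI. Keep the amount removed as a descriptive summary.

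The cost is about one line of wording in each section. Both areas are already to be measured, so no imaging, visit or sample-size change is needed.

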
### Statistical analyses

All statistical analyses will be performed using SAS Enterprise Guide 4 (SAS Institute Inc., Cary, North Carolina, USA). Before performing the main comparative statistical analyses, we will assess whether the baseline variables of the two groups are visually balanced.

An intention-to-treat strategy will be implemented in this non-inferiority RCT. In addition, sensitivity analyses using per-protocol and As-treated will be conducted to identify the deviations from the original assignments during randomization. Participants excluded before or after surgery will not be considered for analysis or replaced, thus avoiding the risk of bias in allocation concealment.

The primary outcome (the ODI score at 12 months post-surgery) will be compared between the two groups. Interlaminar full-endoscopic discectomy will be considered equivalent to microscopic discectomy concerning surgical outcomes if the 95% confidence interval (CI) of the treatment difference value of the Interlaminar full-endoscopic discectomy group is included in the equivalence limit of 12.8 points.

To analyze the time-dependent change in secondary patient-reported and clinical outcomes (i.e., VAS pain scores for the back and lower extremities and ODI, EQ-5D, and POSAS scores), a linear mixed model repeated-measures analysis of variance will be used. Time will be regarded as a categorical variable (at 2 weeks and at 3, 6, and 12 months) and analyzed to evaluate serial changes from baseline, within each group, and between the two groups at each session, with a post hoc test used for any significant time- and group-differences identified.

Chi-square test for categorical variables and Student’s t-test for continuous variables will be used to analyze other clinical and radiographic outcomes and adverse effects between the two groups. The collected data’s distribution will be evaluated using the Shapiro–Wilk test, with a two-sided P-value. Normally distributed continuous variables will be reported as means and standard deviations (SDs), with non-normally distributed continuous variables reported as medians and interquartile ranges. Categorical variables will be reported as count and percentage (%).

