### Sample size justification

In this trial, 100 participants will be recruited, with 50 in each group. Based on previous studies by Copay et al., the non-inferiority margin is 12.8 points and the maximal clinically accepted ODI difference is 12.8 points, with an SD of 17.1 points at 1-year after endoscopic discectomy [21, 35]. Based on the non-inferiority margin of 12.8, 50 participants will be required in each group, with an alpha value of 0.05, a power of 0.90, a one-sided 95% CI, and a loss to follow-up of 20%. Power Analysis and Sample Size software (version 15; NCSS, Kaysville, UT, USA) was used to calculate the sample size.

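### The plan declares intention-to-treat but leaves out randomised participants excluded after surgery, which may bias the 12-month ODI comparison in either direction

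*Protocol article*

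**What the plan says.** All of the analysis-set wording stands in one paragraph of the protocol article, under Statistical analyses:

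- The strategy: "An intention-to-treat strategy will be implemented in this non-inferiority RCT".
- The supporting analyses: "sensitivity analyses using per-protocol and As-treated will be conducted to identify the deviations from the original assignments during randomization".
- The exclusion rule, which follows directly: "Participants excluded before or after surgery will not be considered for analysis or replaced, thus avoiding the risk of bias in allocation concealment".

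The section Randomization and follow-up gives the timing: "After completing the baseline assessments, participants will be block-randomized into either the control (microscopy) or intervention (endoscopy) group, using a 1:1 allocation ratio". Table 1 (Measured outcomes) puts the eligibility check at the screening visit, and randomisation and surgery together at visit 2.

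The analysis affected is the primary one: "The primary outcome (the ODI score at 12 months post-surgery) will be compared between the two groups". The criterion is that the 95% confidence interval "is included in the equivalence limit of 12.8 points". The Blinding section says that surgeons know which procedure was done. No section says on what grounds, by whom or until when a participant may be excluded once randomised.

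**The concern.** Intention-to-treat means that everyone randomised is analysed in the group to which they were assigned. A rule that removes people after randomisation contradicts this, and here it does so in the same paragraph.

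The reason offered does not support the rule. Allocation concealment protects the assignment until it is made. Removing people afterwards cannot protect it, and it opens a route to selection bias. Declining to replace excluded participants is sound. Declining to analyse them is the defect.

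At stake is the comparability of the two groups in the primary comparison. If exclusion after surgery is related to both arm and outcome, the estimated ODI difference is shifted, and the interval is judged against a fixed 12.8-point limit. The paragraph does not restrict the rule to one analysis, so no planned analysis contains everyone randomised.

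**Working it through.** **Step 1. Who is affected.** The order is baseline assessment, randomisation, surgery.

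- Excluded after surgery: always randomised, and already operated on.
- Excluded before surgery: may fall before randomisation (harmless) or between randomisation and surgery (not harmless). The text does not separate the two.

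**Step 2. Whether another planned analysis restores them.** A per-protocol set removes participants, and an as-treated set regroups them by the operation received. Neither adds back people who are not analysed at all.

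**Step 3. The plan's own figure.** Sample size justification: "Based on the non-inferiority margin of 12.8, 50 participants will be required in each group", "with an SD of 17.1 points at 1-year after endoscopic discectomy", power 0.90, 20% loss. The expected difference is taken as 0, because the stated hypothesis is similarity.

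- n per arm = 2 × [17.1 × (1.96 + 1.28) / 12.8]² = 38 at one-sided 0.025 (39 with the t distribution).
- Allowing for loss: 38/0.8 = 48, or 39/0.8 = 49. This agrees with 50 to within two.
- At one-sided 0.05 the result is 31 or 32, inflated to 39 or 40, which does not give 50. That is a separate matter, and the present point does not depend on it. One-sided 0.025, which corresponds to a two-sided 95% interval, is used below.

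**Step 4. Size of the shift.** Let fe and fc be the shares excluded in the endoscopic and microscopic arms. Let D be the excess 12-month ODI of those excluded over those kept, the same in both arms. Each arm's full mean is the mean of those kept plus f × D, so exclusion removes

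shift = D × (fe − fc)

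from the difference (endoscopic minus microscopic). A positive shift favours non-inferiority, because a higher ODI is worse. The article gives no value for fe, fc or D; all are assumptions.

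**Step 5. Consequence.** SE = 17.1 × √(2/40) = 3.82 with 40 per arm after the planned loss. If the true difference equals the margin, the chance of wrongly concluding non-inferiority is Φ(shift/SE − 1.96).

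| Assumed exclusions | D | Shift (ODI points) | Share of margin | False non-inferiority rate |
|---|---|---|---|---|
| Equal in both arms | any | 0 | 0% | 0.025 |
| 3 of 50 vs 0 | 20 | 0.06 × 20 = +1.2 | 9% | 0.050 |
| 5 of 50 vs 0 | 20 | 0.10 × 20 = +2.0 | 16% | 0.075 |
| 15% vs 5% | 15 to 40 | +1.5 to +4.0 | 12% to 31% | 0.059 to 0.180 |
| 5% vs 10% | 20 | −0.05 × 20 = −1.0 | −8% | 0.013 |

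The second and third rows are 0.3 to 0.5 standard errors. With 50 analysed per arm, SE = 17.1 × √(2/50) = 3.42 and the same shifts are 0.35 to 0.58 standard errors.

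**The case against.** The strongest reply is that the article never says who is excluded. A reader might infer that the rule removes surgical failures, such as conversions, recurrences or reoperations, and so pushes the trial towards non-inferiority. The documents do not support that. Infection and recurrence are recorded as adverse events at each follow-up session (Secondary outcomes), which treats those participants as still under follow-up. The planned as-treated analysis presupposes that people who received the other operation remain in the data. Reoperation is not named as a ground for exclusion. The Background does call the endoscopic technique technically harder, but the section on the endoscopic procedure says spine surgeons know the approach, and the Inclusion criteria admit only cases judged suitable for both operations. The last row of the table shows that the bias can also run against non-inferiority.

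A reader might also infer that the intention-to-treat set shrinks almost to the per-protocol set. This is not shown either: if crossovers stay in, the analyses can still differ.

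The sentence may have been meant only for ordinary withdrawals, since non-replacement is typical of withdrawal wording and 20% loss is planned for. This does not rescue it. Loss to follow-up has its own allowance, and setting withdrawn participants aside by rule, including any data they gave, is still not intention-to-treat.

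These replies limit what can be said about direction and size. They leave the contradiction and the mistaken rationale untouched. Nor is this detail that an article may leave to a fuller document: it is a rule that the article states.

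**Conclusion.** The contradiction is certain for participants excluded after surgery and possible for those excluded before it. The stated reason does not justify the rule, and the supporting analyses do not repair it. Surgeons know the arm and no grounds are fixed, so exclusion related to the arm is a credible risk, but it is not a documented effect.

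The size is unknown. Under the assumptions above it runs from about 1 point against non-inferiority, through zero, to 1.2 to 2.0 points towards it. A more unequal pattern (15% vs 5%, D up to 40) reaches 4.0 points. A shift of 1.2 to 2.0 points would double or triple a nominal 0.025 error rate at the margin. Because the rule decides who enters the primary analysis, it should be corrected before the data are unblinded. The need to correct it rests on the contradiction, not on any assumed direction.

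**What to change.** Delete the exclusion sentence together with its rationale, and state instead:

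- All randomised participants are analysed in their assigned group, whatever surgery they received.
- Collection of the 12-month ODI continues after any deviation, unless consent is withdrawn.
- Missing ODI is handled by a pre-specified method, for example the mixed model already planned for repeated ODI.
- No participant is replaced.
- Exclusions apply only to the supportive per-protocol set.

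The cost is a little more follow-up and analysis work. The visits are already scheduled, and phone interviews are already allowed when attendance is impossible. The 50 per arm stands; power at a true difference of 0 and one-sided 0.025 is about 0.96 with 50 analysed per arm and 0.91 with 40. If the mixed model is used, its missing-at-random assumption should be stated.

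Requiring both the intention-to-treat and the per-protocol interval to meet the limit is a separate design choice and is not needed to remove this contradiction.

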### Data collection

After providing informed consent, participants will be enrolled in the study and will undergo baseline assessments, including the following: magnetic resonance images (MRIs), simple radiographs, the Oswestry Disability Index (ODI) score, the EuroQol-5-dimension-5-level (EQ-5D-5L) questionnaire, and the 10-point pain VAS scale, and demographics and baseline patient characteristics [including age, gender, occupation, comorbidity (diabetes mellitus, hypertension), bone mineral density, body mass index, medical/surgical history, smoking/drinking habits, physical examination, and laboratory test]. The assessor will be blinded to participants’ personal information.

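### The 12-month ODI comparison that decides the trial states no baseline adjustment, while a more efficient mixed model for the same ODI data is planned only as a secondary analysis

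*Protocol article*

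**What the plan says.** All of this is in the protocol article.

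- **Primary analysis (Statistical analyses).** "The primary outcome (the ODI score at 12 months post-surgery) will be compared between the two groups". The decision rests on whether the 95% confidence interval of the difference "is included in the equivalence limit of 12.8 points". No test, model or covariate is named. The only stated use of baseline data before this comparison is a visual check of balance.
- **Secondary analysis (same section).** For a list of secondary outcomes that includes ODI, "a linear mixed model repeated-measures analysis of variance will be used", with visit as a categorical factor and between-group comparisons at each visit, 12 months included.
- **Data available.** At entry, "participants will be enrolled in the study and will undergo baseline assessments", ODI among them (Data collection). Table 1 schedules ODI again at 2 weeks and at 12, 24 and 52 weeks.
- **Sample size (Sample size justification).** "the non-inferiority margin is 12.8 points", "with an SD of 17.1 points at 1-year after endoscopic discectomy", "with an alpha value of 0.05", power 0.90 and "a loss to follow-up of 20" percent give 50 per group. The SD is used as it stands, with no reduction for a covariate.

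**The concern.** The article plans two analyses that each give a 12-month group difference in ODI. The one that decides the trial is described as a bare comparison. The one that can use the repeated measurements, and readily takes baseline ODI as a covariate, is kept for secondary purposes.

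Baseline ODI usually predicts later ODI to some degree. Leaving it out of the deciding analysis keeps explainable variation in the error term and widens the interval that is set against 12.8 points. Participants who have 2-week, 3-month or 6-month ODI but no 12-month value would also inform a mixed model, whereas a comparison of 12-month values alone cannot use them. With 20% loss planned for, that could be up to 10 of 50 per group.

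**Working it through.** **Inputs from the documents:** margin 12.8, SD 17.1, power 0.90, loss 20%, 50 per group, so 50 × 0.8 = 40 evaluable per group.

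**Assumptions:** true difference 0; SD 17.1 in both groups; baseline to 12-month correlation r = 0.3 to 0.5; 6- to 12-month correlation ρ = 0.5 to 0.7. The documents give no correlation.

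**Step 1. Reproduce the planned size.** n per group = 2 × [17.1 × (z₁₋α + z₀.₉₀) / 12.8]².

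- One-sided 0.05: 30.6, rounded up to 31; 31/0.8 = 38.75, so 39 per group.
- One-sided 0.025 (equivalent to a two-sided 95% interval): 37.5, rounded up to 38; 38/0.8 = 47.5, so 48 per group. With the t distribution, 39 and 39/0.8 = 48.75, so 49.

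The stated 50 is close to the one-sided 0.025 result, and that level is used below. Both calculations use the raw SD.

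**Step 2. Effect of baseline adjustment with 40 per group.** Residual SD = 17.1 × √(1 − r²); SE = residual SD × √(2/40). Half-width = t × SE with t = 1.991 (78 df, two-sided 95%). Power is from the noncentral t distribution with noncentrality 12.8/SE.

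| r | Variance cut (r²) | Residual SD | SE | 95% half-width | Power, one-sided 0.025 |
|---|---|---|---|---|---|
| 0 | 0% | 17.10 | 3.82 | 7.61 | 0.911 |
| 0.3 | 9% | 16.31 | 3.65 | 7.26 | 0.934 |
| 0.5 | 25% | 14.81 | 3.31 | 6.59 | 0.968 |

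The one degree of freedom spent on the covariate is ignored; it is negligible here. A normal approximation gives nearly the same results: power 0.917, 0.939 and 0.972, and half-widths 7.49, 7.15 and 6.49. At one-sided 0.05, unadjusted power is 0.953 (t) or 0.956 (normal).

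**Step 3. Effect of earlier visits.** If 20% lack a 12-month value and every one of them has a 6-month value, effective n = 40 / (1 − 0.2ρ²).

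- ρ = 0.5: 40/0.950 = 42.1.
- ρ = 0.7: 40/0.902 = 44.3.

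These are upper bounds for the stated correlations, because some lost participants will have no 6-month ODI.

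**The case against.** The strongest reply is that the article is condensed and names no primary model at all. It never calls the analysis unadjusted, and it assigns Student's t-test to other outcomes. Covariates and missing-data handling may be in a full protocol or analysis plan that is not shown. That stands as far as it goes: one cannot assert that baseline ODI will be left out. What remains is what the article does fix, namely that the mixed model is assigned to ODI as a secondary outcome, that baseline is mentioned only for a balance check, and that the sample size uses the raw SD.

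Four stronger readings are tempting, and the documents do not support them:

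- **That participants without a 12-month ODI will be dropped.** This is an inference. The 20% is a sample-size allowance and fixes no analysis method. The sentence leaving some participants out concerns those excluded before or after surgery, not explicitly those lost to follow-up, and it stands beside a statement of intention to treat. How those two statements fit together is a separate question.
- **That earlier ODI visits are ignored.** They enter the secondary model, which contrasts the groups at each visit.
- **That a hospital term is required.** Randomization is described as 1:1 in blocks of four, with no stratification by hospital stated. A hospital term is an option for precision.
- **That chance baseline imbalance biases the result.** Under randomization an unadjusted difference is unbiased, and its interval already allows for chance imbalance. The loss is efficiency.

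It is also fair to say that the trial does not depend on the gain, since unadjusted non-inferiority power with 40 per group already exceeds 0.90.

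**Conclusion.** The point holds as one of efficiency and of which analysis is made primary. As described, a 12-month comparison with no stated baseline adjustment decides the trial, while a better use of the same data is planned as secondary.

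For r between 0.3 and 0.5, adjustment would narrow the half-width by about 0.35 to 1.0 point against a 12.8-point margin and add about 2 to 6 percentage points of power. Earlier visits would add at most about 2 to 4 effective participants per group. They would reduce bias from loss to follow-up only to the extent that the earlier ODI values explain who is lost. Every one of these gains rests on assumed correlations. The planned power for non-inferiority is met without them.

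**What to change.** Name the mixed model that is already planned as the primary analysis:

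- outcome: ODI at 2 weeks and at 3, 6 and 12 months;
- fixed effects: group, visit, group-by-visit, baseline ODI and baseline-by-visit;
- unstructured covariance across visits;
- decision: take the 12-month group difference and its confidence interval from this model and compare it with the 12.8-point margin.

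A hospital term may be added for precision. The choice should be fixed before any unblinded outcome data are seen. The sample size can stay as it is, since it is adequate without the adjustment.

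The cost is wording in the protocol and analysis plan. The measurements and the type of model are already planned. If an analysis plan already specifies this for the primary outcome, only the protocol text needs to be aligned with it.
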